## Psychometric analyses

Psychometric assessment for this study focuses on post-hoc quantitative analyses of the SCHEMA trial’s primary and secondary outcome measures, particularly to inform the choice of preference-based measure which may be the most ‘appropriate’ for the economic evaluation (see the ‘Economic evaluation’ and ‘Discussion’ sections) and therefore conducted before starting the economic evaluation. In this case, we are specifically interested in the primary outcome measure for the SCHEMA trial (i.e. MOAS score) and those measures which can be used to produce utility scores used to estimate QALYs (i.e. EQ-5D-3L and ReQoL-UI, self-reported and proxy-reported); the BSI PSDI will also be included, but the primary comparison is with the MOAS.

In terms of psychometric properties, the focus will be on the construct validity and responsiveness of the utility scores, as the psychometric properties specified of interest to NICE within their technology appraisal methods guide [42]. Such psychometric analyses have been used to support economic evaluations previously [43, 44].

### Construct validity focussed on convergent and known-group validity

Construct validity assesses the extent to which a measure reflects HRQoL differences hypothesised to exist. We assess construct validity in relation to convergent and known-group validity.

Convergent validity assesses the relationship between measures, proposed here to be based on correlation analyses and locally weighted scatterplot smoothing (LOWESS) techniques. For example, Spearman’s rank absolute correlation strength (ACS) coefficient and associated p-value are proposed as a non-parametric test (with the actual method chosen post hoc based on the measures’ score distributions) which indicates the degree to which instruments are measuring related factors [45]. LOWESS can complement the correlation analyses as a form of non-parametric regression which plots a line of central tendency between two variables on a scatterplot, thereby visualising their general relationship across the possible score ranges without making assumptions about the actual relationship [46].

Known-group validity assesses the extent to which instrument scores differ between groups that are expected to differ, measured using Cohen’s d standardised absolute effect sizes (AES i.e. the difference in mean scores between two adjacent severity subgroups divided by the standard deviation of scores for the milder of the two subgroups) [45, 47]. For example, this will include stratification of the trial participants at each time point based on the MOAS MCID threshold of 5 points, regardless of trial arm. The non-parametric Kruskal Wallis test complements assessing AES to suggest if there is a statistically significant difference between the two (or more) known groups.

### Responsiveness

Responsiveness is important in economic evaluation as any change in health must be reflected by a change in utility/preferences and a subsequent change in QALYs. To measure responsiveness, we will examine floor (worst possible score) and ceiling (best possible score) effects, which affect the ability of the measure to detect deterioration or improvements in health, respectively. We will also examine the magnitude of change in scores over time as a crude indicator of responsiveness; however, we will cross-reference change in measure scores against changes on the MOAS (i.e. those achieving an MCID of 5 points or not).

### Additional considerations: responder perspective and face validity

There are additional considerations which can’t be assessed quantitatively but are stated here as they will be considered narratively. As the MOAS is completed by site research-staff, whereas the EQ-5D-3L and ReQoL-10 are completed by the trial-participant and ward staff (proxy), these different reporter perspectives will be narratively considered within the psychometric analyses [48, 49]. Additionally, from a self-reported perspective by the trial-participant, it is perceived that the adapted EQ-5D-3L will have face validity whereas the ReQoL-10 may not and this impacts on the trustworthiness of the self-reported scores. These considerations will inform the interpretation and description of the psychometric results.

## Economic evaluation

Cost-effectiveness analysis via cost per quality-adjusted life year (QALY) is recommended internationally, including by the National Institute for Health and Care Excellence (NICE) for England and Wales [42]. Therefore, in adults within secure care who have borderline to mild/moderate ID, we will calculate the mean incremental cost per QALY of interpersonal art psychotherapy compared to usual care over 38 weeks, from a healthcare perspective.

Cost-effectiveness will be inferred when comparing our incremental cost-effectiveness results to a relevant cost-effectiveness threshold, such as thresholds from £0 (whereby cost savings are preferred to QALY gains) up to £50,000 per QALY, with specific attention to £20,000 to £30,000 per QALY thresholds as suggested by NICE [42].

The primary QALY-based analyses will use the self-reported, adapted EQ-5D-3L, albeit its use has implications/complications (see the ‘Discussion’ section). To calculate QALYs, the area-under-the-curve (AUC) will be calculated using the data collected for the EQ-5D-5L and ReQoL-UI at baseline, 19 weeks, and 38 weeks [50].

The economic evaluation will be conducted on an ITT basis, based on guidance by Hunter et al. [50] and Franklin et al. [23]. To calculate mean incremental costs and QALYs, both observed and (regression) adjusted mean values will be estimated and compared [44]. Choice of regression model for the adjusted analyses will follow the choices also made for the statistical analyses of the primary outcome (e.g. generalised linear-mixed models) as will the choice of other covariates, while also considering the relevant prognostic nature of the covariate to the economic evaluation outcomes of interest (e.g. baseline utility for QALYs) [50].

Incremental cost-effectiveness ratios (ICERs) will be calculated based on incremental costs over incremental QALYs as the estimated mean difference between the two trial arms. The ICER represents the cost per QALY of the intervention-arm compared to control-arm which will be compared to a relevant cost-effectiveness threshold to infer ‘cost-effectiveness’ or not.

Bootstrapping will be used to estimate standard errors and confidence intervals and generate cost-effectiveness planes and cost-effectiveness acceptability curves (CEACs). Cost-effectiveness planes will be used to present the dispersion of the estimated ICERs following resampling with replacements as part of the bootstrapping process, over 5000 resampled iterations. The CEACs will be used to visualise and report on the probability of cost-effectiveness across a range of cost-effectiveness threshold values (e.g. up to £50,000 per QALY).

Missing data, sensitivity, and sub-group analyses will align with that proposed for the primary statistical analyses for which there is also an interest related to the economic evaluation.

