### Analysis of primary outcome

The aim of the primary analysis is to examine the effectiveness of art psychotherapy in reducing the frequency and severity of aggressive incidences compared to usual care, as measured by the change in MOAS score from baseline to week 19 post-randomisation. The distribution of the MOAS scores will be assessed graphically using histograms and the mean (SD) or median [IQR] of the change in score from baseline to week 19 will be tabulated overall and by trial arm (art psychotherapy versus usual care). The change of primary outcome from baseline to week 19 will be assessed graphically using a scatter plot.

The primary outcome analysis will be performed on an ITT basis. Initially, we will use a linear mixed-effect regression model [27, 28], with the week-19 MOAS score as the dependent variable and the randomisation group as the independent variable, adjusted for the baseline MOAS score, random effect of the variable indexing strata based on gender and diagnosis of psychosis. In addition, we anticipate potential clustering in the intervention arm due to therapists. We will examine this by the ICC from the linear mixed-effect model and if there is a considerable amount of heterogeneity in the primary outcome associated with therapists, we will adjust the effect estimate for the partial clustering due to therapists. For this, both partially homoscedastic and heteroscedastic regression models will be explored, and we will report the results as appropriate. The homoscedastic model assumes between-cluster variability is only present in the intervention arm and the individual level variation is the same in both arms. The heteroscedastic model assumes between-cluster variability is only present in the intervention arm but allows different individual level variation in intervention and control arms [29, 30]. From the initial model(s), we will present the estimated difference in MOAS score at week-19 for the intervention group compared to the control group with 95% CI.

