### Alternative methods if distributional assumptions not met

If the data does not meet the distributional assumptions of linear mixed-effects regression, the data will be transformed if possible (e.g. log with base 10). If transformations do not improve the distributions of scores, non-parametric/semi-parametric statistical methods or dichotomising the outcome scores will be considered. Non-parametric methods include generalised estimating equations (GEE) [31–33], quantile regression [34], and bootstrapping [35]. If a dichotomous/categorical version of an outcome is used, mixed-effect logistic [36] or multinomial logistic regression [37] will be considered.

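### The adjusted cost and QALY models inherit the model chosen for MOAS; some of its fallbacks do not estimate the mean differences from which the plan defines the ICER

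*Protocol article*

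**What the plan says.** The Economic evaluation section of the protocol article sets its target as a mean: "we will calculate the mean incremental cost per QALY of interpersonal art psychotherapy compared to usual care over 38 weeks". It repeats this for the estimates, "To calculate mean incremental costs and QALYs, both observed and (regression) adjusted mean values will be estimated and compared", and builds the ICER from "incremental costs over incremental QALYs as the estimated mean difference between the two trial arms". The result is read against cost-effectiveness thresholds, with particular attention to £20,000 to £30,000 per QALY.

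The rule for the adjusted model comes in the same section: "Choice of regression model for the adjusted analyses will follow the choices also made for the statistical analyses of the primary outcome". The example in brackets is generalised linear mixed models. Covariates are to follow the primary analysis too, "while also considering the relevant prognostic nature of the covariate to the economic evaluation outcomes of interest". That qualifier concerns covariates and does not reach the model family or the scale.

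For MOAS, the Analysis of primary outcome section starts from a mean-based model: "Initially, we will use a linear mixed-effect regression model". The Assumption checking section has the score distributions examined before analysis, by plots and the Shapiro–Wilk test. If the assumptions fail, the section on alternative methods says "the data will be transformed if possible (e.g. log with base 10"), and if that does not help, "non-parametric/semi-parametric statistical methods or dichotomising the outcome scores will be considered". The non-parametric methods it names are GEE, quantile regression and bootstrapping. For a dichotomised or categorical outcome it names mixed-effect logistic and multinomial logistic regression.

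**The concern.** The model for costs and QALYs is tied to a decision made on a different variable. MOAS is a weighted count of aggressive incidents over one week with a floor at zero. Its shape gives no information about which model suits 38-week costs or QALYs.

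The tie also runs through fallbacks that change what is estimated. A log10 model yields a ratio of geometric means, quantile regression at the median a difference in medians, and logistic regression an odds ratio. None of these is the difference in mean pounds or mean QALYs that the ICER needs before it can be compared with a threshold per QALY.

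If such a fallback were chosen for MOAS, the analysts would have to break one of two sentences in the same section: the one requiring adjusted means, or the one requiring the MOAS model. The plan does not say which prevails. They would decide after seeing the data, which is what a pre-specified plan is meant to avoid.

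**Working it through.** The plan states no figure on this point to reproduce. The check traces the rule through the sections and then illustrates the possible size.

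**Step 1. Does each MOAS route give a mean difference when carried over to costs or QALYs?**

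| Route open to MOAS | What it estimates for costs or QALYs | Usable directly in the defined ICER? |
|---|---|---|
| Linear mixed model, including the homoscedastic and heteroscedastic therapist models | Adjusted mean difference | Yes |
| GEE, identity link | Adjusted mean difference | Yes |
| Bootstrapping of a mean-based model | Mean difference; only the interval changes | Yes |
| GLMM with a non-identity link | Effect on the link scale | Only with marginal predictions, which are not mentioned |
| log10 transform | Ratio of geometric means | No, not without retransformation, which is not mentioned |
| Quantile regression (median) | Median difference | No |
| Dichotomised outcome, logistic or multinomial | Odds ratio or similar | No |

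The conflict therefore needs two things: MOAS leaves the linear mixed model, and the replacement is one of the routes that does not return means.

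**Step 2. Is there an exemption?** The only economic qualifier in the rule is about covariates. The 5000 bootstrap resamples are for standard errors, confidence intervals, cost-effectiveness planes and acceptability curves. They describe uncertainty around whatever the model estimates and do not alter the estimand. No exemption was found.

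**Step 3. How far can the estimands differ?** The documents give no cost or QALY distribution, so everything here is assumed: log-normal costs, control median £10,000, QALY gain 0.03.

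For a log-normal variable with log-SD s, mean = median × exp(s²/2). The ratio of mean to median is:
- s = 0.5: exp(0.125) = 1.13
- s = 0.8: exp(0.32) = 1.38
- s = 1.0: exp(0.50) = 1.65

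*Case A: equal medians, s = 0.8 control and 1.0 intervention.*
- log10 coefficient = 0; median difference = £0.
- Mean difference = 10,000 × (exp(0.50) − exp(0.32)) = £2,716.
- Ratio of means = exp(0.50 − 0.32) = exp(0.18) = 1.197, a 20% difference.
- Per QALY: 2,716 / 0.03 ≈ £90,500, against £0 from the median.

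*Case B: log-SDs reversed.* Log and median models again show no difference. The mean difference is −£2,716.

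*Case C: equal log-SDs of 0.8, median ratio 1.1.*
- Median difference = £1,000, or 1,000 / 0.03 ≈ £33,300 per QALY.
- Mean difference = 10,000 × 0.1 × exp(0.32) = £1,377, or about £45,900 per QALY.
- The ratio of arithmetic means equals the ratio of geometric means (1.1), so here a log model is recoverable by retransformation. The median difference in pounds is still not the mean difference.

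For a dichotomised outcome there is no cost or QALY difference to put into the ratio.

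**The case against.** The strongest reply is that the section should be read as a whole. The sentence just before the rule asks for adjusted mean values, and the following paragraph defines the ICER from mean differences, so a sensible analyst would carry over only a model that returns means. The plan's own example, generalised linear mixed models, points the same way, since that family includes models that give natural-scale means through marginal predictions. The rule also does not cite the fallback section. It can be read as pointing to the primary analysis section alone, whose strata and therapist-clustering structure is natural to share. The fallbacks are worded tentatively: transform if possible, other methods to be considered. Observed mean costs and QALYs are reported beside the adjusted ones, so a divergence could be noticed.

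Much of this stands, and it is why the point is conditional. It does not remove the point. The demand for means is one side of the conflict and does not say which sentence yields. The example is only an example, and a GLMM with a non-identity link still needs a step that the text does not mention. The distributional fallbacks apply expressly to the primary outcome, so they are among the choices made for it.

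A reader might infer more: that the plan commits costs and QALYs to log, quantile or dichotomised models, or that the reported ICER will not be a ratio of mean differences. The documents do not support that. The starting model is linear, several fallbacks preserve means, and adjusted means are explicitly promised. A reader might also object that logs fail for QALYs at or below zero, which the stated utility minima (−0.594 for EQ-5D-3L, −0.195 for ReQoL-UI) permit. The wording that data are transformed only if possible largely covers that.

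**Conclusion.** The point holds in conditional form. The plan defines the adjusted ICER through mean differences and, in the same section, ties its regression model to a MOAS choice that may end in a method that does not directly estimate mean differences. This is a fault in a stated rule, not a complaint that model detail is missing.

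Its size cannot be derived from the documents. Under the assumed log-normal costs, the discrepancy runs from a 20% difference in mean cost that a log or median model misses entirely (in either direction) to a gap of about £12,600 per QALY (45,900 − 33,300) when only the median is reported. These figures rest on the chosen log-SDs, the £10,000 median and the 0.03 QALY gain. They show that the choice of estimand can matter against a £20,000 to £30,000 threshold; they do not predict this trial's result.

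How likely the trigger is cannot be stated either. Zeros and right skew are plausible for a one-week incident score, but the documents give no MOAS distribution. The observed ICER is untouched in every case. A correction before analysis is worthwhile, but the economic evaluation as a whole is not undermined.

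**What to change.** Replace the sentence on model choice with one that says the following:

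- Cost and QALY models are chosen from the cost and QALY data, independently of any distributional fallback used for MOAS.
- They always report adjusted arithmetic mean differences on the natural scale, for example from a linear model, or a GLM with marginal predictions, with the planned 5000 bootstrap resamples.
- They keep the strata and therapist-clustering structure of the primary analysis, and baseline utility as a covariate for QALYs.

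The cost is one sentence of plan wording and standard models in the software already named. No stated number changes. The small downside is that the economic and clinical models may differ in form, which the report can explain in a line.

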## Statistical software

Statistical analysis will be carried out using Stata (StataCorp LLC, TX, USA) version 17 or higher.

## Discussion

This paper presents the detailed SHEAP for SCHEMA trial, which is a two-arm, parallel-group, single-blind, individually randomised controlled trial of effectiveness, comparing manualised interpersonal art psychotherapy to usual care. The main objective is to assess the effectiveness and cost-effectiveness of interpersonal art psychotherapy (compared to usual care) in reducing the frequency and severity of aggressive behaviour in adults in secure care. This SHEAP is aimed to evaluate the effect of intervention on primary and secondary outcomes with an adjustment for the pre-planned covariates in mixed effect linear regression models. We will analyse data on an intention-to-treat basis and use datasets generated by multiple imputations using chained equations to assess the effect of missing observations on the analyses if required. In addition, we will conduct a per-protocol analysis which will include only those participants who adhere to the intervention.

The SHEAP will minimise the risk of outcome reporting bias as having a predefined plan will minimise the risk of data-driven analyses. We strengthen our results by replacing missing observations with imputed values from multiple imputations by chained equations, facilitating calculation of unbiased estimates, standard errors and confidence intervals.

It is worth mentioning here that the proxy EQ-5D-3L and ReQoL-10 questionnaires completed by the ward staff at baseline, 19 and 38 weeks post-randomisation will be completed by a member of staff who is familiar with the participant’s general health; however, it may not always be completed by the same person, so we will record who has conducted each assessment. The variability in who completes the questionnaire could introduce measurement bias or inter-rater variability, which might affect the reliability and validity of the proxy EQ-5D-3L outcome. The ICC could be calculated to quantify the degree of agreement between nurses, and an exploratory sensitivity analysis could include the research nurse as a random effect in the primary analysis.

The study has found it harder to recruit participants than anticipated and has led to a slower recruitment rate. An 80% power was approved by the NIHR and resulted in a reduction in the required sample size. However, it is anticipated that the study may not achieve the current target sample size of 75 participants per arm. Due to the smaller sample size, we could have wider confidence intervals, reflecting greater uncertainty about the true effect size; as such, results may need to be interpreted with this in mind. However, we have planned to use bootstrap techniques to compute the bootstrap confidence intervals for the effect estimates and report them.

For the economic analysis, the primary HRQoL measure for estimating QALYs is the self-reported, adapted EQ-5D-3L. The rationale is that the self-reported, adapted EQ-5D-3L best aligns with the current NICE methods for technology appraisal guidelines and has been developed specifically for people with learning disabilities. However, there are complications within this patient population that might mean that although NICE prefers the EQ-5D-3L and the adapted version has face validity in the patient population (i.e. those with learning disabilities), it might not be the most appropriate measure to use for the economic analysis; therefore, psychometric analyses are proposed to inform the preferred outcome for the economic analyses. The use of psychometric analyses means the choice of outcome measure for the economic analysis will be chosen post-hoc (albeit, the psychometric analyses will be completed before conducting the economic evaluation); however, as post-hoc choices can allude to data/outcome mining (e.g. making the results fit the preferred outcome), this post-hoc choice does not change the primary outcome for the economic analyses which will remain the adapted, self-reported EQ-5D-3L. Rather, the psychometric analyses results will be published alongside the economic analyses, with the economic analyses results, discussion and conclusion informed by the psychometric analyses to suggest which outcome measure has the best psychometric performance and therefore may be the more ‘appropriate’ outcome for the economic analysis, despite the primary outcome remaining the adapted, self-reported EQ-5D-3L.

Finally, this analysis plan is comprehensive, which includes a detailed statistical and health economic analysis plan coupled with an appropriate psychometric evaluation of the measures. We believe that application of this SHEAP will reduce the risks of outcome reporting bias and data-driven results, facilitating an unbiased evaluation of the trial data and supporting confidence in our findings.

